**Methods and analysis:**

We will analyse publicly available quarterly vaccine uptake data (between April 2019 and March 2025) from the Cover of Vaccination Evaluated Rapidly programme for general practices (GPs) in England. The intervention group will be defined as practices located within a 1 km radius of the intervention sites. A synthetic control group will be constructed using non-intervention GPs matched on pre-intervention vaccine uptake, and linked demographic, socioeconomic and healthcare capacity covariates. Primary outcomes are the uptake of MMR1 and MMR2 vaccines. Secondary outcomes include the uptake of 6-in-1, PCV and rotavirus vaccines. Average treatment effects will be estimated as the post-intervention difference in uptake between intervention and synthetic control groups. Sensitivity analyses will examine spillover effects, alternative spatial definitions of exposure, the biasing effect of concurrent interventions and the feasibility of analysis at small area neighbourhood level.

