**Ethics and dissemination:**

This study will be conducted as part of the ReCITE project, which has received ethical approval from the Liverpool School of Tropical Medicine Research Ethics Committee (Reference: 24–018) and is funded by the UK Arts and Humanities Research Council (Project Number: AH/Z505341/1). Findings will be shared with the project funder and submitted for publication in a peer-reviewed journal.

STRENGTHS AND LIMITATIONS OF THIS STUDYTo our best knowledge, this will be among the first UK-based studies to use synthetic control methods for evaluating the impact of community-led intervention on childhood vaccine uptake.The Cover of Vaccination Evaluated Rapidly dataset used will provide a near universal coverage of children registered with a general practice in England, offering a large pool for constructing a robust synthetic control group.The study is sustainable, providing methodological transparency through plans to publish analytic code and any derived data, enabling replication and adaptation for future evaluation of similar community-led interventions across England.Despite our attempt to include a large set of covariates, there remains a potential for residual confounding from unobserved characteristics, such as parental vaccine attitudes, language barriers and undocumented outreach.The absence of a UK registry for reporting local childhood vaccination initiatives may limit our ability to identify other concurrent interventions affecting vaccine uptake in the control practices, potentially affecting the quality of matching and impact estimation.

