### Analysis

We will use the SCM, an observational quasi-experimental approach that extends the traditional difference-in-differences (DiD) framework,^27^ to estimate the impact of the intervention on childhood vaccine uptake. While DiD assumes that the intervention and comparison groups would have followed parallel trends in the absence of the intervention, SCM constructs a weighted combination of untreated units, called a ‘synthetic control’, that mirrors the pre-intervention characteristics and outcome trends (ie, vaccine uptake) of the intervention units.^28^ This allows for a more robust estimation of the counterfactual, particularly when the parallel trends assumption is unlikely to hold. This method has been previously used to evaluate the population-level impact of various public health interventions,^34 35^ including those targeting vaccine uptake,^36 37^ demonstrating its suitability for the current study.

GPs will serve as our unit of analysis, with the target population being registered children aged under 5 years who were eligible for routine childhood vaccinations between April 2019 and March 2025, as reported in the COVER dataset. The intervention group is defined as practices whose population-weighted centroids fell within a 1 km radius of any of the nine intervention sites. As such, 19 practices will be included in the intervention group (see figure 2), with all remaining practices in England forming the donor pool for constructing the synthetic control group. We will apply SCM for microdata,^38^ which is specifically suited to settings involving numerous small scale units, such as GPs. Matching will be performed using calibration weights for the pre-intervention uptake of included vaccines and the previously mentioned covariates. The final inclusion of covariates in the SCM will also be guided by their practical contribution to achieving balance between intervention and control units.

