### Sensitivity analysis

Given the community-based nature of the intervention, there is potential for spillover effects beyond the identified intervention practices. To mitigate this effect, we will conduct a sensitivity analysis excluding other non-intervention GPs located within the central and north Liverpool PCNs from the donor pool practices used to construct the synthetic control group. We will also incorporate a one-quarter lag at the start of the post-intervention period (ie, starts at Q20 instead of Q19) to allow sufficient time for any changes in vaccine uptake to become observable.

To assess the sensitivity of the estimated effect to the exposure’s spatial definition, we will test alternative buffer distances (0.5 km, 1.5 km and 2 km) from intervention event sites. We will further attempt to exclude practices that may have been affected by other concurrent vaccine-related initiatives implemented elsewhere in England. To identify such initiatives, an audit of interventions form will be distributed to immunisation leads at the UK Health Security Agency and to public health leads across the nine local authorities in Cheshire and Merseyside via the Champs Public Health Collaborative. A copy of the form is provided in online supplemental material 1.

Further sensitivity analyses will involve adjusting the pre-intervention period to begin after the final phase of national COVID-19 restrictions in England (February 2022 to Q12 in our dataset), as it could bias the counterfactual estimation. For example, tiered restrictions during the pandemic varied in stringency across England. This has led to regional variation in childhood vaccine uptake^40^ and will consequently affect the SCM matching.

In addition, we will rerun the evaluation using vaccine uptake aggregated to a small area neighbourhood level (LSOA), which may better reflect the community-based nature of the intervention. Finally, to test the robustness of our findings, we will explore alternative approaches to constructing synthetic controls. These may include methods that incorporate negative control series or rely on different assumptions about the counterfactual.

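### The concurrent-initiative sensitivity analysis deals with donor practices, but no analysis is stated for other vaccine initiatives that reached the 19 treated practices

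*Protocol article*

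**What the plan says.** The abstract lists, among the matters that the sensitivity analyses will examine, "the biasing effect of concurrent interventions and the feasibility of analysis at small area neighbourhood level". It does not limit this to one arm.

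The Sensitivity analysis section gives the rule: "We will further attempt to exclude practices that may have been affected by other concurrent vaccine-related initiatives implemented elsewhere in England". To find such initiatives, an audit form goes to immunisation leads at the UK Health Security Agency (UKHSA) and to "public health leads across the nine local authorities in Cheshire and Merseyside via the Champs Public Health Collaborative".

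The strengths and limitations box after the abstract says that the lack of a UK registry "may limit our ability to identify other concurrent interventions affecting vaccine uptake in the control practices".

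The Analysis section fixes the two groups: "As such, 19 practices will be included in the intervention group", "with all remaining practices in England forming the donor pool for constructing the synthetic control group". The effect is the mean difference in uptake, treated minus synthetic control, over Q19 to Q24. The Timeline section places the audit in January to April 2026, before analysis starts.

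**The concern.** Another vaccine initiative can distort the comparison from either side. In donors it raises the synthetic control and hides part of a real effect. In treated practices it raises the treated mean and looks like an effect of HELP. The stated check deals with the first case. For the second, no analysis drops, flags or adjusts any of the 19 practices.

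The study asks what HELP did. The treated practices lie close together in one city, in areas chosen for low uptake and high deprivation, so one further local programme could reach many of them at once. HELP ended on 1 June 2024 and the post-intervention period runs to March 2025, so three of the six post quarters (Q22 to Q24, July 2024 to March 2025) fall wholly after it. At stake is whether a positive result can be attributed to HELP or only to HELP together with whatever else was happening locally.

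**Working it through.** **1. Scope of the rule.** The exclusion concerns initiatives elsewhere in England, the strengths and limitations box speaks of control practices, and the donor pool is every other practice in England. Together these make the check donor-side. The spillover analysis also removes donors only. The audit reaches the Cheshire and Merseyside authorities (assumed to include Liverpool), so it could return initiatives in treated practices, but no use of such returns is stated.

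**2. Bias algebra.** The article gives no figure to reproduce here. Write

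estimate = τ + c − w·d

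where τ is the HELP effect, c the mean post-period lift in treated practices from other initiatives, w the synthetic-control weight on exposed donors, and d the post-period lift in those donors. Donor exclusion sets w to 0 and leaves c untouched.

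**3. Size of c.** c = share of treated practices exposed × effect. Both inputs are assumptions:
- 0.25 × 2 = 0.5 points
- 0.50 × 5 = 2.5 points
- 1.00 × 5 = 5.0 points

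The Expected results section anticipates 5 to 15 points, so the middle case is half of the lower end (2.5 / 5).

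**4. Size of the donor term.** With assumed w of 0.05 to 0.30 and d of 2 to 5, exclusion adds 0.05 × 2 = 0.1 to 0.30 × 5 = 1.5 points. Example with τ = 0, c = 2, w = 0.10, d = 5: before exclusion 0 + 2 − 0.5 = 1.5; after it 2.0. The donor bias is gone and all of c remains.

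**5. Does exclusion always move the estimate the same way?** Weights are calibrated to the pre-intervention period, so removing donors changes the remaining weights. A simplified simulation refitted non-negative weights after exclusion (200 donors, 19 treated practices, 18 pre and 6 post quarters, 150 replicates per setting, no covariates, true HELP effect 0):

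| Initiative in exposed donors | Donors exposed | Mean shift (points) | Runs shifting down |
|---|---|---|---|
| +2 points after Q18 | 5 / 10 / 20% | +0.09 / +0.21 / +0.40 | 8 / 5 / 2% |
| +5 points after Q18 | 5 / 10 / 20% | +0.23 / +0.51 / +0.99 | 1 / 0 / 0% |
| No effect | 5 / 10 / 20% | +0.01 / 0.00 / −0.01 | 47 / 52 / 49% |
| +5 points in Q11 to Q18, then gone | 5 / 10 / 20% | −0.18 / −0.29 / −0.50 | 99 / 94 / 97% |

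The direction therefore depends on when the other initiative acted and whether it worked. With a 3-point lift in all treated practices and in 10% of donors, the estimate went from 2.67 to 2.97. Exclusion removed the donor bias and left the treated-side 3 points in place.

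**6. Do other planned elements cover c?** Permutation reassigns treatment among control units, so it does not identify a local programme shared by the treated cluster. The secondary vaccines may, by the article's own account, respond to community engagement, so they cannot isolate HELP. Negative control series are mentioned only as a possibility.

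**The case against.** The strongest reply is that the donor-only scope is inferred. The exclusion sentence refers to practices without naming an arm, whereas the spillover sentence names the donor pool outright. The audit form is in a supplement not shown here, and coding of its returns is the sort of detail that an article leaves out. The article also concedes that undocumented or local outreach may confound and that the audit may miss initiatives; the Limitations section does not confine this to controls. This stands in part: the scope is a reading, though the natural one, and the general limitation is disclosed. But the article does state the rule and where it applies, and a disclosed limitation is not an analysis of it.

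Three stronger readings are tempting, and the documents do not support them.

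- A reader might infer that the check can move the result only toward a HELP effect. The weights are refitted, and initiatives that did nothing or faded before Q19 can move the estimate down. Where donors truly gained after Q18, removing them repairs a bias toward the null and is not a fault.
- A reader might infer that the authors expect other initiatives in the treated area. The Introduction reports a measles cluster in Liverpool, which is disease and not a programme. The ReCITE interventions in the Discussion carry no dates and are not tied to the 19 practices.
- A reader might infer that the audit's reach is misdescribed, because local authority leads are asked only in one region. The phrase about England says where initiatives took place, not how fully they were audited; UKHSA leads are asked too, and incompleteness is conceded.

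**Conclusion.** The point holds in a limited form. As worded, the check handles donor contamination and leaves co-interventions in the treated practices without any stated analysis, although the abstract promises to examine concurrent interventions without limiting this to one arm. Any lift from another initiative in treated practices that began after Q18 would remain in the main and the sensitivity estimates alike. A stable effect from before Q19 would largely be absorbed by the pre-period matching.

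The size is unknown. The 0.5 to 5.0 points rest wholly on assumed shares and effects, and the upper end needs every treated practice to have had a second initiative worth 5 points. The gap is in what the study can attribute to HELP; it is not an error in the main model. It merits correction because the information is about to be collected and the remedy is cheap.

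**What to change.** Before analysis starts:

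1. Use the audit returns from UKHSA and from Cheshire and Merseyside to code each of the 19 treated practices for other vaccine initiatives and their dates, with the same definition of exposure as for donors. Confirm that Liverpool is among the authorities asked.
2. Report how many treated practices were exposed, and in which quarters.
3. Add one sensitivity run that leaves out exposed treated practices alongside exposed donors, with weights refitted. Treated practices left out should not enter the donor pool.
4. If all or nearly all treated practices were exposed, word the conclusion as the effect of HELP plus concurrent local activity.

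This needs no new recipients or data: one coding column and one further model run. The drawback is fewer treated practices and a wider null distribution. For example, with 10 of the 19 left, the spread grows by about √(19/10) = 1.38 if practices vary independently and equally (an assumption). That run also describes a smaller set of practices, so a change from the main estimate may partly reflect a different HELP effect in them.

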## Methods and analysis

### Data sources and measures

#### Vaccine uptake

This study will use publicly available data from the Cover of Vaccination Evaluated Rapidly (COVER) programme,^29^ which provides quarterly statistics on the uptake of routine childhood immunisations for children aged 5 years and under at the general practice (GP) level in England.

Our primary outcome is the uptake of the first and second doses of MMR vaccine (MMR1 and MMR2). We will further examine the 6-in-1 vaccine, PCV booster dose and rotavirus vaccine as secondary outcomes, as they are administered at similar ages and often coincide with MMR. Table 1 provides information on the age at which each vaccine is administered, based on the UK childhood vaccination schedule,^30^ and its corresponding COVER reporting age.

**Table 1 T1:** Childhood vaccines included in the analysis, with their recommended administration ages and corresponding measurement points in the COVER dataset

Vaccine	Age administered	Age measured in COVER
DTaP/IPV/Hib/ HepB (6-in-1)	8, 12, 16 weeks	12 months
Rotavirus	8, 12 weeks	12 months
PCV booster	13 months	2 years
MMR1	13 months	2 years, 5 years
MMR2	3 years 4 months	5 years

COVER, Cover of Vaccination Evaluated Rapidly; DTaP, diphtheria, tetanus, pertussis; HepB, hepatitis B; Hib, haemophilus influenzae type B; IPV, inactivated polio vaccine; MenC, meningococcal group C; MMR, measles, mumps and rubella; PCV, pneumococcal conjugate vaccine.

COVER reports vaccine uptake as the percentage of eligible children who received the vaccine by a certain age within a given quarter. A key strength of this dataset is its completeness, with a near universal coverage across the GP-registered child population in England. We will use data spanning 24 consecutive quarters, from April 2019 (the earliest quarter with GP-level data) to March 2025, labelled sequentially from Quarter 1 (Q1) to Quarter 24 (Q24).

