**Figure 2 F2:**
[figure not shown]
Coverage of MMR1 at 2 years and MMR2 at 5 years across Liverpool by MSOA in the year preceding the intervention (April 2022 to March 2023). Red dots with green circles represent the locations of intervention events with a 1 km surrounding buffer, and cyan dots represent the population-weighted centroid of intervention GPs. Coverage data are based on GP-level uptake reported through the COVER programme. COVER, Cover of Vaccination Evaluated Rapidly; GP, general practice; MMR, measles, mumps and rubella; MSOA, Middle Layer Super Output Area.

The pre-intervention period spans Q1 to Q18 (April 2019 to September 2023), with Q19 to Q24 (October 2023 to March 2025) defining the post-intervention period. The average treatment effect will be estimated as the average difference in vaccine uptake between the intervention and synthetic control groups in the post-intervention period.

The statistical significance of estimated effects will be assessed using the permutation inference, following the method described by Robbins and Davenport.^39^ We will perform 250 permutations, reassigning treatment status to control units to generate a distribution of treatment effects under the null hypothesis (ie, no difference in vaccine uptake between the intervention and control groups). All analyses will be conducted using R V.4.4.2 and the microsynth package.^39^

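### The COVID-19 sensitivity analysis cuts the pre-period by calendar quarter and ignores the COVER lag, so for MMR2 at 5 every retained quarter still holds children due before restrictions ended

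*Protocol article*

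**What the plan says.** The Analysis section sets the main matching window: "The pre-intervention period spans Q1 to Q18 (April 2019 to September 2023"). The Sensitivity analysis section then proposes "adjusting the pre-intervention period to begin after the final phase of national COVID-19 restrictions in England (February 2022 to Q12 in our dataset"). Its reason is that "tiered restrictions during the pandemic varied in stringency across England", and it continues: "This has led to regional variation in childhood vaccine uptake", which it expects to carry into the matching. The same cut applies to every vaccine.

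The Vaccine uptake section defines the COVER measure as the "percentage of eligible children who received the vaccine by a certain age within a given quarter". Table 1 gives the due and measured ages. MMR1 is due at 13 months and measured at "2 years, 5 years". MMR2 is due at 3 years 4 months and measured at 5 years. The PCV booster is due at 13 months and measured at 2 years. The 6-in-1 and rotavirus courses finish at 16 and 12 weeks and are measured at 12 months. MMR1 and MMR2 are the primary outcomes.

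**The concern.** A COVER quarter identifies when children reached the measured age, not when they were due the dose. A cut at the calendar end of restrictions therefore does not remove the cohorts whose doses fell due during them. The longer the lag between due age and measured age, the more of those cohorts stay in the matching window. The sensitivity analysis section does not mention this lag.

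The risk is one of interpretation. If the truncated and full analyses agree, that will naturally be reported as showing that regional pandemic disruption did not distort the synthetic control. For MMR2, a primary outcome, that inference would rest on a matching window made up of the cohorts the check was meant to set aside, with most of the pre-pandemic cohorts discarded. Disagreement would be equally hard to interpret.

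**Working it through.** **Inputs.** Quarters are "labelled sequentially from Quarter 1 (Q1) to Quarter 24 (Q24") from April 2019, so quarter k starts 3(k − 1) months after April 2019. The end of restrictions, February 2022, is in the protocol. The start is not; March 2020 is assumed, with October 2020 as the alternative.

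**The plan's own labels.** Q12 starts 33 months after April 2019 and covers January to March 2022, so February 2022 does fall in Q12. Q18 covers July to September 2023, as stated.

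**Formula.** Due month = month of reaching the measured age − (measured age − due age). For 6-in-1 and rotavirus the last scheduled dose is used: 16 weeks ≈ 3.7 months and 12 weeks ≈ 2.8 months.

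| Outcome | Lag (months) | Due months, Q12–Q18 | Quarters wholly due March 2020 to February 2022 | Mixed | Wholly after |
|---|---|---|---|---|---|
| MMR2 at 5 | 60 − 40 = 20 | May 2020 – Jan 2022 | Q12–Q18 (7 of 7) | none | none |
| MMR1 at 2, PCV | 24 − 13 = 11 | Feb 2021 – Oct 2022 | Q12–Q15 (4 of 7) | Q16 | Q17–Q18 |
| MMR1 at 5 | 60 − 13 = 47 | Feb 2018 – Oct 2019 | 0 of 7 | none | none (all due before) |
| 6-in-1 | 12 − 3.7 = 8.3 | about May 2021 – Jan 2023 | Q12–Q14 (3 of 7) | Q15 | Q16–Q18 |
| Rotavirus | 12 − 2.8 = 9.2 | about Apr 2021 – Dec 2022 | Q12–Q14 (3 of 7) | Q15 | Q16–Q18 |

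**If the start is Q13.** MMR2 becomes 6 of 6 and MMR1 at 2 becomes 3 of 6.

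**First clean MMR2 quarter.** Q19 (October to December 2023) was due February to April 2022 and is mixed. Q20 (January to March 2024) was due May to July 2022 and is the first wholly later quarter. The post-period begins at Q19.

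**What the cut discards for MMR2.** Q10 (July to September 2021) was due November 2019 to January 2020, so Q1 to Q10 were all due before March 2020. Q11 was due February to April 2020 and straddles that date. All eleven are dropped with a Q12 start.

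**Sensitivity to the assumed start.** With restrictions counted only from October 2020, MMR2 has 16 of 21 due months inside them (76%) from Q12, or 16 of 18 (89%) from Q13. For MMR1 at 2 the share is 12 or 13 of 21 (57–62%) from Q12, or 9 or 10 of 18 (50–56%) from Q13, under either start; the range depends on whether February 2022 is counted.

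**Catch-up time after February 2022**, for a child reaching the measured age in mid-quarter:

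- MMR2: Q13 2.5/20 = 13%; Q15 8.5/20 = 43%; Q16 11.5/20 = 58%; Q18 17.5/20 = 88%.
- MMR1 at 2: Q13 2.5/11 = 23%; Q14 5.5/11 = 50%; Q15 8.5/11 = 77%; Q16 onwards 100%.
- MMR1 at 5: none were due in restrictions, but with a March 2020 start between 23.5 (Q12) and 24 (Q18) of the 47 months overlapped them, about half.

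**The case against.** The strongest reply is that uptake counts any dose given up to the measured age, so the due month is not the whole of exposure. By Q18 most of the MMR2 catch-up window lies after February 2022, and for MMR1 at 2 the last two retained quarters are clean even by due date. The retained quarters are therefore graded in exposure. The protocol says only that the pandemic period could bias the counterfactual; it does not promise restriction-free birth cohorts. This stands. A reader might infer that the check can test nothing, and the documents do not support that.

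Three other stronger readings also fail:

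- **MMR1 as a whole is mostly affected.** The protocol measures MMR1 at 5 as well as at 2, and no retained cohort at 5 was due during restrictions. At 2 the share is a modest majority from Q12 and about half from Q13.
- **The window wrongly opens before restrictions ended.** The parenthesis may only locate February 2022 within Q12, in which case starting afterwards means Q13. The fair criticism is ambiguity.
- **The funding covariate is lost.** Table 2 lists it for 2019 to 2021, but nothing says that shortening the outcome window removes a baseline covariate, and final covariate inclusion is left to balance.

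It is also true that this is one of several sensitivity analyses and does not change the primary estimate. None of this gives MMR2 a pandemic-free matching window or makes one calendar cut suit all outcomes.

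**Conclusion.** The point holds in a limited form and should be addressed. As fixed, the check is a weak, partial test of pandemic disruption. It is weakest for MMR2 at 5, where all retained quarters were due before restrictions ended and no start quarter within the pre-period would change that. It is moderate for MMR1 at 2 and PCV, and for 6-in-1 and rotavirus, where the later retained quarters are clean. MMR1 at 5 is affected only through catch-up time.

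That every retained MMR2 cohort was due before restrictions ended rests only on the protocol's dates and Table 1. That they were all due during restrictions, and that Q1 to Q10 are pre-pandemic, also needs the assumed March 2020 start. Agreement between the truncated and main analyses should not be reported as robustness to pandemic disruption for MMR2.

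**What to change.** 1. State the start quarter of the truncated pre-period unambiguously (Q12 or Q13).
2. Define the exclusion by due date for each outcome where a clean start exists: Q17 for MMR1 at 2 and PCV, Q16 for 6-in-1 and rotavirus. Disclose that this leaves only 2 and 3 matching quarters respectively.
3. State that no restriction-free pre-period exists for MMR2 at 5, and that retained MMR1-at-5 cohorts were due before the pandemic but had catch-up windows overlapping it.
4. For the regional mechanism the protocol names, add a run that keeps the full pre-period and limits donors to practices with a restriction history similar to Liverpool's. The sponsor should choose and justify the area, because the protocol gives no data on which areas shared that history.

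The cost is revised wording, one donor filter and separate matching runs per outcome. The restricted donor pool will be smaller and balance may be poorer, and two or three matching quarters give little protection against a chance match. By the Timeline section, analysis starts only after the audit planned for January to April 2026, so the change can be made before any results are seen.
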